**Figure 1 F1:**
[figure not shown]
Participant flowchart for Fracturein the Elderly Multidisciplinary Rehabilitation—phase III (FEMuR III).

### Trial setting and selection of sites/clinicians

Sites were recruited by coinvestigators in different regions of England and Wales with a spread of socioeconomic conditions and a mixture of rural and urban locations: Kent (CS), Merseyside (NW), Norwich ([name]), North Wales (RL), Nottingham (PL) and South Wales (MB). The sites had to include trauma centres treating proximal femoral fracture and links to community rehabilitation teams, which could accommodate the extra community rehabilitation sessions.

Patients will be recruited on orthopaedic, rehabilitation and community hospital wards or after hospital discharge home. The intervention will be delivered in the community, following hospital discharge, by community teams receiving referrals from the acute hospital sites and their associated community hospitals.

#### Selection of sites/clinicians

Sites have been opened to recruitment in Nottingham, Norfolk, North Wales, South Wales and East Kent. Further sites are planned in west Kent, Derby and Cheshire plus others. The site trial teams comprise principal investigators, hospital and community NHS staff, research assistants and support staff from clinical research networks.

### Trial population

#### Inclusion criteria

Age 60 years or older.Recent proximal femoral fracture.Surgical repair by replacement arthroplasty, hemiarthroplasty or internal fixation.Living in their own home prior to hip fracture.Living and receiving rehabilitation from the NHS in the area covered by the trial sites.

#### Exclusion criteria

Living in residential or nursing homes prior to hip fracture.Participants unable to understand English or Welsh.Lacking mental capacity to give informed consent.

#### Carer participants

We will also recruit carer participants to evaluate carer strain, anxiety and depression. These are defined as a relative or friend providing help with activities of daily living or physical care, at least 4 days a week. Carer participants will provide informed consent but will not receive any trial intervention, so will not undergo eligibility screening or randomisation.

### Trial treatment/interventions

We plan to compare an enhanced rehabilitation intervention with usual rehabilitation care.

#### Usual rehabilitation care

Usual care consists of a multidisciplinary rehabilitation delivered by the acute hospital, community hospital and community services depending on patients’ individual needs at different times during their recovery and on the availability and accessibility of services in different areas. The multidisciplinary team delivering care and rehabilitation may include: orthopaedic surgeons, orthogeriatricians, nurses, physiotherapists, occupational therapists, dieticians, pharmacists, general practitioners (GPs) and social workers. The settings for care include acute orthopaedic or orthogeriatric wards, rehabilitation units in community hospitals, rehabilitation beds in care homes, the patient’s own home and care home settings, all delivered by a variety of community teams in both health and social care services. There will be no restrictions on concomitant medications or treatments.

#### Enhanced rehabilitation

The main aim of the intervention is to enhance usual rehabilitation by increasing patients’ self-efficacy^25^ and increasing the amount and quality of patients’ practice of physical exercise and activities of daily living to improve functional outcomes at follow-up. Self-efficacy will be enhanced by means of a patient-held information workbook and a goal setting diary. The workbook will include:

Information about what has happened to them and what to expect from their recovery.Information about NHS, council and voluntary sector services including falls’ prevention programmes.How to manage their recovery, set goals and monitor progress of their rehabilitation; reduce fear of falling.

In addition to whatever community-based rehabilitation is provided as part of usual care, we will provide up to six additional therapy sessions, once patients are discharged home. These can be delivered by physiotherapists, occupational therapists or their assistants, who have been trained to deliver these extra sessions alongside the workbook, using the diary to set goals and monitor progress. The therapists will tailor these extra sessions, so that the total number of sessions used, the time scale for their delivery and the sessions’ content will vary between patients according to need but may include the practice of specific exercises and activities of daily living. Throughout the running of this trial, therapists will receive on-going support via emails, newsletters and refresher events.

### Outcomes

Patient participants will complete outcome measures at baseline, 17 and 52 weeks administered by a research assistant blinded to participant allocation. Follow-up assessments will be completed within participants’ homes (tables 1 and 2). The primary outcome will be the difference in NEADL scale^26 27^ at 52-week follow-up, between the usual rehabilitation arm and the enhanced rehabilitation arm. At baseline, the patient will be asked to recall the 4 weeks prior to hip fracture and not 4 weeks prior to completing this questionnaire. Secondary outcomes will include the Hospital Anxiety and Depression Scale (HADS),^28^ economic measures will be EuroQol, EQ-5D-3L^29^ and Client Service Receipt Inventory.^30^ A reduced version of this will be used at baseline to reduce participant burden as they recover from hip fracture surgery. Potential mediators of outcome will include a Visual Analogue Scale (VAS) for hip pain intensity,^31^ Falls Efficacy Scale—International (self-efficacy)^32 33^ and Visual Analogue Scale—Fear of Falling (VASFoF).^34^

**Table 1 T1:** Outcome measures

Patient completed measures—primary	Description	Range
Nottingham Extended Activities of Daily Living scale^26 27^	Activities of daily living (mobility, kitchen, domestic, leisure) with higher score indicating greater independence	(0–66)
**Patient completed measures—secondary**		
Hospital Anxiety and Depression Scale (HADS)^28^	Anxiety and depression in patients with physical health problems. Two subscales (0–21) with higher score indicate greater anxiety or depression	(0–21)
**Patient completed economic measures**		
EuroQol EQ-5D-3L^29^	Health utility index with five dimensions (mobility, self-care, usual activities, pain/discomfort, anxiety/depression) and three levels to give health states converted to a utility weight. Also Visual Analogue Scale (VAS) for health state today	Health utility weight from 0 (death) to 1.0 (perfect health) also with negative values VAS (0–100)
Client Service Receipt Inventory 30	Use of health and social care services	According to activity
**Patient completed process measures (potential mediators of outcomes**)		
Visual Analogue Scale (VAS) for hip pain intensity^31^	VAS of current hip pain intensity	(0–10 cm)
Falls Efficacy Scale— International (self-efficacy)^32 33^	How concerned a patient is about falling when performing 16 activities of daily living both inside and outside of the home, rated from 1 (not at all concerned) to 4 (very concerned)	(16–64)
VAS-Fear of Falling^34^	VAS with higher scores indicating greater fear of falling	(0–10 cm)
**Assessment of cognitive function**		
Abbreviated Mental Test Score^35 36^	Detecting and monitoring cognitive impairment. 10 items with lower scores indicating worse cognitive function	(0–10)
**Objective measures of physical function**		
Grip strength^37^	Hand dynamometer	According to metre reading
Short Physical Performance Battery^40 41^	Physical function tests assessing lower limb function in terms of balance, gait, strength and endurance. Higher score indicates greater function	(0–12)
**Carer completed measure—secondary outcome**		
Caregiver Strain Index^42^	13 items in the domains: employment, financial, physical, social and time. Positive responses to seven or more items indicate a greater level of strain	(0–13)
HADS^28^	Anxiety and depression in carers. Two subscales (0–21) with higher score indicate greater anxiety or depression	(0–21)

**Table 2 T2:** Fracturein the Elderly Multidisciplinary Rehabilitation—phase III (FEMuR III) protocol schedule of forms and procedures

Procedures	Screening	Baseline/randomisation*	Trial intervention†	17 weeks postrandomisation follow-up	Qualitative interviews	52 weeks postrandomisation follow-up
Eligibility screening and consent						
Assessment of eligibility criteria	X					
Written and informed consent (patient/carer)	X					
Confirm consent		X	X	X	X	X
Randomisation		X				
Discharge data		X				
Outcome measurement— patient						
Nottingham Extended Activities of Daily Living		X		X		X
Hospital Anxiety and Depression Scale (HADS)		X		X		X
Abbreviated Mental Test Score		X		X		X
Visual Analogue Scale (VAS) hip pain intensity		X		X		X
Falls Efficacy Scale—International		X		X		X
Visual Analogue Score—Fear of Falling		X		X		X
EuroQol-5D-3L		X		X		X
Client Service Receipt Inventory		X		X		X
Grip strength		X		X		X
Short Physical Performance Battery				X		X
Outcome measurement— carer						
Caregiver Strain Index		X		X		X
HADS		X		X		X
Trial intervention†			X			
Qualitative interviews						
Re-affirm consent verbally specifically for qualitative phone interview. (patient/carer)					X	
Qualitative telephone interview					X	
Safety event reporting						
Monitoring of adverse events			X	X	X	X
Monitoring of serious adverse events			X	X	X	X

Participant follow-up visits should take place at 17 (±2 weeks) and 52 (±2 weeks) weeks postrandomisation.

*Randomisation and baseline should take place no later than 6 weeks after hip fracture repair surgery.

†If randomised to intervention arm.

The research assistant will assess patient participants’ cognitive function at baseline, 17 and 52 weeks using the Abbreviated Mental Test Score.^35^ The research assistant will measure physical function at baseline, 17 and 52 weeks using the grip strength test^36–38^ and using the Short Physical Performance Battery^39 40^ at 17 and 52 weeks.

Carer participants will complete the Caregiver Strain Index^41^ and the HADS^28^ at baseline, 17 and 52 weeks.

Qualitative interviews will take place with patients and carers after 17 weeks. These will gather data on trial participation and intervention design (see the Process evaluation below).

Routinely collected demographic, clinical and recruitment data will include the numbers of patients who are eligible, willing to be randomised, withdraw after randomisation, complete outcome measurements, also reasons for non-completion, age, gender, hip fracture type, surgery type, comorbid conditions, place of residence prior to admission and place of discharge.

### Sample size calculation

The phase II feasibility study results^23^ informed the sample size calculation. The adjusted mean difference in the primary outcome measure (NEADL) between the intervention and control group in the feasibility trial was 3.0. Work completed by Wu *et al*^27^ has suggested that the minimum clinically significant difference is 2.4; this has been used within the sample size calculation for this phase III RCT. A two-point score in the NEADL scale would equate to an improvement in function from being independent around the home to being able to use public transport or get in and out of a car. The adjusted mean difference between the groups in NEADL in the randomised feasibility study had an SD of 5.8. In this multisite phase III RCT, a more diverse sample would be expected, so a larger SD would be expected. Parker *et al*^42^ used NEADL in a rehabilitation RCT and found an SD of 10. Based on the analysis of covariance (ANCOVA) with alpha of 5% and 90% power to detect a difference of 2.4 (SD=10, R^2^ of covariate=0.52), 352 patient participants would be required to complete the trial over both treatment groups. When considering the 79% retention rate in the feasibility study,^23^ the trial would need to recruit 446 patient participants.

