## Methods and analysis

### Trial design

This is a pragmatic, multisite, parallel-group, two-armed, superiority RCT with 1:1 allocation ratio and an internal pilot phase (figure 1). Outcome assessment and statistical analysis will be blinded; patient and carer participants and clinicians will be unblinded. A concurrent economic evaluation will be a cost-utility analysis from a health service and personal social care perspective. An embedded process evaluation will examine the mechanisms and processes that explain the implementation and impacts of the enhanced rehabilitation programme. The RCT was registered on 23 November 2018. Trial registration data can be found in online supplemental appendix 1.

10.1136/bmjopen-2020-039791.supp1Supplementary data

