#### Analysis of effectiveness

Primary and secondary outcomes at baseline, 17 weeks’ and 52 weeks’ follow-up will be summarised for each treatment group using descriptive statistics at each time point. If normally distributed, the difference between group means (with 95% CIs) will be reported from the ANCOVA adjusted for baseline score and stratification factors.

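### The 90% power and the stated ANCOVA make no allowance for similarity of outcome among intervention patients who share a therapist or team; if there is any, power is overstated and the standard error too small

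*Protocol article*

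**What the plan says.** The Sample size calculation section sets the target: "Based on the analysis of covariance (ANCOVA) with alpha of 5% and 90% power to detect a difference of 2.4" ("SD=10, R^2^ of covariate=0.52"). It concludes that "352 patient participants would be required to complete the trial over both treatment groups". The only inflation is for the 79% retention seen in the feasibility study, so that "the trial would need to recruit 446 patient participants". It mentions no ICC, design effect or number of therapists. The design is a "superiority RCT with 1:1 allocation ratio and an internal pilot phase".

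Under Analysis of effectiveness, the difference between group means is to come from the "ANCOVA adjusted for baseline score and stratification factors". No therapist or team term is named. The Randomisation procedures section does not list the minimisation factors, so it is not known whether site is among them.

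On delivery, the Enhanced rehabilitation section says of the up to six extra sessions: "These can be delivered by physiotherapists, occupational therapists or their assistants, who have been trained to deliver these extra sessions". It adds: "The therapists will tailor these extra sessions", so that their number, timing and content differ between patients according to need. The Trial setting section places delivery with community teams that take referrals from the acute sites. Under Process evaluation data collection, therapists are to be interviewed midway through their involvement and again at the end, to see what they learn over time. The Usual rehabilitation care section says that usual care, too, is delivered partly by community teams.

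**The concern.** Patients are randomised individually, but the added treatment in one arm reaches them through a group of therapists. The plan to study each therapist's learning over the trial suggests that a therapist will treat several patients in turn. If some therapists or teams achieve more than others, outcomes of patients who share one are correlated, and 176 intervention patients carry less information than 176 independent ones.

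Adjusting for stratification factors would not fully deal with this. Even if site is one of them, a site term removes what is common to both arms at that site, not differences between therapists within the intervention arm.

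Two things are at stake: whether the trial has the power it states for its primary outcome, and whether the 95% CI from the ANCOVA has its nominal coverage.

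**Working it through.** **Inputs from the protocol article.** Difference 2.4, SD 10, covariate R² 0.52, alpha 5%, power 90%, 1:1 allocation, retention 79%. Sidedness is not stated; a two-sided test reproduces the figure, while a one-sided test would give 286.

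**Reproducing the stated figures.**

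- Residual SD = 10 × √(1 − 0.52) = 6.928.
- n per arm = 2 × (1.960 + 1.2816)² × 100 × 0.48 / 2.4² = 175.1, rounded up to 176, so 352 in total.
- 352 / 0.79 = 445.6, so 446.
- Standard error with 176 per arm = 6.928 × √(2/176) = 0.7385. Then 2.4 / 0.7385 = 3.249 and power = Φ(3.249 − 1.960) = 90.1%.

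Both totals match with no design effect, so they contain no allowance for clustering.

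**Inputs that must be assumed.** The documents give no ICC and no therapist count. I take 15, 30 or 45 therapists (T) sharing 176 intervention completers equally, and an ICC of 0.01 or 0.05 for the covariate-adjusted outcome. Each patient belongs to one therapist, with clustering in the intervention arm only.

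**Formulas.**

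- Patients per therapist: m = 176 / T.
- Variance inflation in the intervention arm: 1 + (m − 1) × ICC.
- Overall design effect: DE = [1 + 1 + (m − 1) × ICC] / 2.
- True standard error / independence standard error = √DE.
- Power of a test that allows for the clustering: Φ(3.249/√DE − 1.960).
- Type I error of the ANCOVA that ignores it: 2 × [1 − Φ(1.960/√DE)].

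**Example, T = 30, ICC 0.05.** m = 5.87; DE = (2 + 4.87 × 0.05)/2 = 1.122; √DE = 1.059. Power = Φ(3.068 − 1.960) = 86.6%. Type I error = 2 × [1 − Φ(1.851)] = 6.4%.

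| Therapists | m | ICC | DE | SE ratio | Power | Type I error |
|---|---|---|---|---|---|---|
| 45 | 3.9 | 0.01 | 1.015 | 1.01 | 89.7% | 5.2% |
| 30 | 5.9 | 0.01 | 1.024 | 1.01 | 89.4% | 5.3% |
| 15 | 11.7 | 0.01 | 1.054 | 1.03 | 88.6% | 5.6% |
| 45 | 3.9 | 0.05 | 1.073 | 1.04 | 88.0% | 5.8% |
| 30 | 5.9 | 0.05 | 1.122 | 1.06 | 86.6% | 6.4% |
| 15 | 11.7 | 0.05 | 1.268 | 1.13 | 82.3% | 8.2% |

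The last two columns describe different tests: power is for an analysis that holds its 5% level, type I error is for the ANCOVA as stated. The normal approximation ignores the limited degrees of freedom when therapists are few, so it slightly flatters the power.

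**Larger caseloads.** With 20 patients per therapist (176/20 = 8.8 therapists) and ICC 0.05, DE = (2 + 19 × 0.05)/2 = 1.475, power is 76.3% and the nominal 95% CI covers about 89.3%. At ICC 0 nothing changes.

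**The case against.** The strongest reply is that the clustering is inferred. The article gives no caseload, and a patient with up to six sessions may see several staff, so strict nesting in one therapist is not established. Tailoring follows the patient's need, which does not by itself make a therapist's patients alike. Community teams also deliver usual care to both arms. If the same staff treat controls, variation common to both arms does not shrink the standard error of the treatment difference, and treating controls as unclustered would be wrong. All of this stands. It is why the point is conditional and why the model below must be adaptable.

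A second reply is that a therapist effect may be set out in the full protocol or in a SAP that is not shown. That also stands for the model: silence in one sentence of a condensed article is not an error. It does not rescue the power statement, which the article makes itself. If a therapist effect is planned elsewhere and the ICC is positive, the 90% does not describe that analysis.

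A reader might infer that the CI is certainly too narrow and that type I error certainly exceeds 5%. The documents do not support this. If the extra sessions change nothing for anyone, they create no clustering. Inflation needs therapist effects that vary around a zero average, or caseloads that already differ, and adjustment for site could absorb part of the latter. Nor do the documents show that the primary ANCOVA must be replaced.

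Finally, retention was 83% at submission. If that held to 52 weeks, 446 × 0.83 gives about 370 completers. With 185 per arm, 30 therapists and ICC 0.05, power would be about 88%: better, but still below 90%.

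**Conclusion.** The point holds in conditional form. The sample size is exactly the independent-patient figure, and the stated ANCOVA names no term for therapist or team, although one arm's extra treatment is delivered and tailored by therapists. For any positive ICC within therapist or team in that arm, stated power is too high and the ANCOVA standard error too small.

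The size rests on assumed inputs. With 15 to 45 therapists, the effect is negligible at ICC 0.01 (power 88.6–89.7%, type I error 5.2–5.6%). It is worth attention at ICC 0.05 (about 82–88% and 5.8–8.2%), and greater with larger caseloads. This justifies a qualified power statement and a prespecified analysis. It does not show that the trial is underpowered.

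**What to change.** 1. In the Sample size calculation, state that 90% power assumes no therapist clustering. Add power over an assumed range of ICCs and caseloads, such as the table above, with the assumptions labelled. Leave enrolment at 446.
2. Record the lead therapist or community team for each intervention patient. The section on intervention delivery and adherence says that the session form captures length and content, but mentions no therapist identifier, so confirm that it does or add one. Define the lead therapist for patients seen by several staff, or use the team as the cluster.
3. Prespecify, at least as a sensitivity analysis to the primary ANCOVA, a partially nested mixed model. It should have the same fixed effects, a random lead-therapist or team effect in the intervention arm, controls as singletons, and Satterthwaite or Kenward–Roger degrees of freedom. If the same staff also treat control patients, adapt the random structure. Report the estimated ICC.

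The cost is a few lines of text, a small amount of data linkage, a slightly less favourable power statement and possibly a slightly wider CI. No extra patients or visits are needed.

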### Recruitment and randomisation

#### Screening and consent—patient participants

Patients with proximal femoral fracture will be identified and screened for eligibility, including mental capacity, by clinical staff on orthopaedic or rehabilitation wards. If the patients are eligible, and interested in the trial, the trial team researchers would then recruit patients following the trial’s informed consent process. Assessment of eligibility may occur over an extended period, if, for example, the patient is experiencing temporary delirium postsurgery. If, during this period, patients are transferred to rehabilitation wards, community hospitals or discharged home, then assessment will continue in these alternative locations. These assessments will be recorded in a screening log, including any reasons for ineligibility.

#### Informed consent—carer participants

For the purpose of this RCT, carers are defined as either a relative or friend caring for a hip fracture patient, helping them with activities of daily living or physical care on at least 4 days a week. They will be identified and recruited following the trial’s informed consent process. Copies of the participant information sheets and informed consent forms are found in online supplemental appendix 1.

#### Randomisation procedures

Patient participants who provide informed consent will complete baseline outcome measurements prior to randomisation. Randomisation will take place no later than 6 weeks after hip fracture repair surgery. The randomisation will have an allocation ratio of 1:1 within each stratum and across the trial. Randomisation will use a minimisation programme with a built-in random element using factors that will not be made known to individuals in charge of recruitment to minimise any potential for predicting allocation. Randomisation will be completed by secure web access to the remote randomisation site at the clinical trial unit. The therapists delivering the enhanced rehabilitation intervention will receive an automated email when a participant has been allocated to the intervention group.

